### 3.2.2 Secondary Endpoints

- To compare safety of the two anesthetic techniques we will document rates of moderate and severe AEs, device-related malfunctions, occurrence of device displacement, and time to complete clinical wound healing
- To compare ease of use of the topical vs. standard injection technique for local anesthesia during Shang Ring circumcision, we will document dwell time required for onset of adequate anesthesia with the topical cream and time to adequate anesthesia with injectable anesthesia, potency of anesthesia provided by both techniques, and problems encountered during anesthesia with the two techniques.
- We will also explore service optimization in terms of determining how to best sequence and group patients for Shang Ring circumcision given the dwell time necessary for topical anesthetic effect.
- To compare duration of post-procedural analgesic effects between the topical vs. injectable anesthesia groups, we will document reported pain at various time points such as 1 and 24 hours post-circumcision between the two groups using the VAS.
- To compare satisfaction with topical vs. injectable anesthetic, we will interview study participants and their parents or legally acceptable representative (LAR) as appropriate to document acceptability and satisfaction with the circumcision, the Shang Ring procedure, post-procedure pain, and time to return to normal activity between the two techniques
- To compare satisfaction with the topical vs. injectable anesthetic among clinical providers in the study, we will interview them about their experiences, acceptability and satisfaction with the two anesthetic techniques

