The injectable approach shall utilize a combination of a penile and a ring block with 1% lidocaine injected with a small gauge needle. This is the standard anesthesia approach used in the Kenya VMMC program. The maximum amount of lidocaine administered will be 4.5 mg/kg. Onset of action typically requires 3 to 10 minutes. The topical approach shall consist of applying EMLA cream to the both the inside and outside surfaces of the foreskin. The anesthetic will then be allowed to dwell for up to 45 minutes for onset of action, with appropriate adjustments made based on the run-in described in the previous paragraph.

In both the injectable and topical anesthetic groups, we will test for numbness using the approach that is currently used, i.e. using blunt forceps on all of the quadrants of the penile shaft, on both the cutaneous and the mucosal sides to determine if anesthesia has taken effect. If it is determined that anesthesia has not taken effect in any participant in the topical group, we will resort to injectable anesthesia.

The Wong-Baker FACES Visual Analogue Scale (VAS) shall be used for pain assessment as we have done in our previous Shang Ring studies (Barone et al., 2011; Barone et al., 2012; Barone et al., 2013, Sokal et al., 2014).

The immediate complications of the circumcision procedure will be recorded on either an Adverse Event (AE) or Serious Adverse Event (SAE) form and may include such findings as: excessive pain, excessive bleeding, anesthetic-related complications, excessive swelling, excessive skin removal, and damage to the penis (e.g. injury to the glans or urethra). Data on procedure times and surgical difficulties, including problems with use of Shang Ring shall also be collected.

Participants will be instructed to return to the study site if they experience medical events such as severe discoloration of the penis, signs of infection (purulence), severe or increasing pain, or any other significant concern that they may have.

Study staff will contact participants or their parents/LAR if appropriate by mobile phone call and/or SMS to remind them of their next follow-up visit. All reasonable efforts will be made to contact those who do not return for follow-up visits. If necessary home visits may be resorted to especially in the case where the ring has not yet been confirmed at the site to have been removed or the client has an AE.

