All other endpoints will be summarized by anesthetic technique and compared between groups using either two-sample t-tests or chi-squared tests, as appropriate for the endpoint, all conducted at the two-sided 0.05 significance level. We will not make any adjustments for multiple comparisons. 95% confidence intervals for differences between groups will be presented. Missing data will be assumed to be missing in random fashion and ignored.

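### Time to adequate anesthesia in Phase II is set for a t-test with missing values ignored; if any topical participants never become numb, the topical mean is taken over successes only

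*Combined protocol and SAP*

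**What the plan says.** Section 3.2.2 (Secondary Endpoints, Phase II) sets out the ease-of-use comparison: "we will document dwell time required for onset of adequate anesthesia with the topical cream and time to adequate anesthesia with injectable anesthesia". The next item in that list explores how to sequence and group clients given the dwell time.

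Section 8.2, under Phase II, sets the limit: "The anesthetic will then be allowed to dwell for up to 45 minutes for onset of action". The run-in may lead to changes in that limit. Every participant is tested for numbness before surgery. For those who are not numb: "If it is determined that anesthesia has not taken effect in any participant in the topical group, we will resort to injectable anesthesia".

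Section 9.2 (Analysis Plan Summary) gives the analysis. Endpoints other than pain and adverse events are grouped by technique and are to be "compared between groups using either two-sample t-tests or chi-squared tests". Each test is two-sided at the 5% level. The same section treats missing data as randomly missing and ignores them, and bases the primary Phase II analyses on the anesthesia actually received. The only method it names that handles censoring is Kaplan-Meier, for Phase I wound healing. Nothing says how a topical participant who never became numb enters the dwell-time comparison.

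**The concern.** For a topical participant who is converted, the onset time is not missing at random. It is known to exceed the time he waited. A t-test that ignores missing values drops him, so the topical mean describes only participants for whom the cream worked in time. The worse the cream performs, the more slow onsets are removed.

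Grouping by technique can add a second distortion. If technique means what was received, the converted participant moves to the injectable group. If his clock then starts at cream application, he also lengthens the injectable mean. The plan states neither how he is grouped for this endpoint nor how he is timed.

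At stake is the ease-of-use comparison, and any reading of its topical mean as the waiting time a program should expect.

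**Working it through.** **Stated figures.** The plan gives no figure for dwell time. Its nearest figure is the 100% power for pain in Section 9.1 (difference 1, SD 1.8, 2:1, two-sided 0.05). That reproduces at 99.5% with 100 vs 200 and 99.8% with 115 vs 230, and does not bear on this point.

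**Inputs from the documents.** Dwell limit L = 45 minutes (Section 8.2). Topical arm of 230, which is two thirds of 345 (Section 9.1). Injectable onset of 3 to 10 minutes (Section 8.2).

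**Assumed, because the documents give neither.** Onset is lognormal with median m of 20, 30 or 35 minutes and log-SD s of 0.4 or 0.5.

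**Formulas.** Let a = (ln L − ln m)/s.
- Share not numb by L: f = 1 − Φ(a).
- Mean among those numb by L: M = m·exp(s²/2)·Φ(a − s)/Φ(a).
- Mean restricted to L, with failures kept at L: R = (1 − f)·M + f·L.
- Selection effect: R − M = f·(L − M). This identity holds for any distribution and is above zero whenever f is.

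**One case in full** (m = 30, s = 0.4). a = 0.405/0.4 = 1.014, so f = 0.155. M = 32.50 × 0.730/0.845 = 28.1. R − M = 0.155 × (45 − 28.1) = 2.6 minutes.

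**Adding the test schedule.** If numbness is tested every d minutes, the recorded onset is the first multiple of d at or after true onset. The net error is the mean recorded time among those numb by L, minus R. Negative means understated. The interval d is assumed: Section 8.2 gives 3 to 5 minutes as an example for the run-in only.

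| m | s | Not numb by 45 | M | R | R − M | Net, d = 3 | Net, d = 5 |
|---|---|---|---|---|---|---|---|
| 20 | 0.4 | 2.1% | 21.0 | 21.5 | 0.5 | +1.0 | +2.0 |
| 20 | 0.5 | 5.2% | 20.8 | 22.1 | 1.3 | +0.2 | +1.2 |
| 30 | 0.4 | 15.5% | 28.1 | 30.7 | 2.6 | −1.1 | −0.2 |
| 30 | 0.5 | 20.9% | 26.7 | 30.5 | 3.8 | −2.3 | −1.4 |
| 35 | 0.4 | 26.5% | 30.4 | 34.3 | 3.9 | −2.4 | −1.4 |
| 35 | 0.5 | 30.8% | 28.7 | 33.7 | 5.0 | −3.5 | −2.6 |

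With d = 15 the net error is an overstatement in all six settings, by 2.1 to 6.9 minutes.

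**Cross-check against the full, unrestricted mean** (lognormal, CV 0.3 to 0.5). With 10% not numb (23 of 230), the mean of those numb is 2.2 to 3.3 minutes too low. With 20% (46 of 230), it is 4.2 to 6.6 minutes too low.

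**Effect on the injectable group.** Suppose 23 converted participants are counted as injectable and timed from cream application, each with 45 minutes plus an injectable onset of 6.5 (the midpoint of 3 to 10). The injectable mean becomes (115 × 6.5 + 23 × 51.5)/138 = 14.0 minutes instead of 6.5.

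**The case against.** Several points on the other side have force.

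- **The failure rate is unknown and may be near zero.** Section 1.2 reports adequate anesthesia in China with dwell times of 15 to 45 minutes, and Section 8.2 expects the cream to be adequate. With no failures there is no selection. The rows with 26% to 31% failing are less likely to persist, because Section 8.2 allows the dwell time to be adjusted or another agent explored. This stands: the point is conditional.
- **The net direction is not fixed.** Frequent testing is planned only for the first 10 topical participants in each age group (20 of 230) and any injectable participants in that period. After that no test interval is given. A reader might infer that the reported dwell time will be understated. The table shows that late recording can cancel or reverse this, so the documents do not support it.
- **The planning figure has another source.** A reader might infer that the program's minimum dwell time would be set too short. Section 8.2 ties that minimum to the run-in testing, not to this t-test. Nor is the finding that cream takes longer than injection likely to change, given 15 to 45 minutes against 3 to 10.
- **The plan is a summary.** Section 9.2 promises a detailed plan, lets the test depend on the endpoint, and will show where as-treated and intention-to-treat differ. That would reveal conversions. But the choice it offers is between two tests, neither of which handles censoring, and no replacement is in the documents supplied.
- **Staff might enter 45 minutes for a failure.** The mean would then equal R, with no error against the restricted mean. The plan does not say to do this, and its missing-data rule points the other way.

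**Conclusion.** The point holds in conditional form. As written, the rules would compare time to adequate anesthesia among participants for whom the allotted method worked, and would ignore onset times that are absent because onset was slow or never came. If any topical participant is converted, that selection lowers the topical mean by f·(L − M): about 0.5 to 1.3 minutes at 2% to 5% failing and 2.6 to 3.8 minutes at 16% to 21%, on assumed lognormal onset and a 45-minute limit. The limit may change after the run-in, but any finite limit raises the same issue. The net error in the reported mean could have either sign, depending on how often numbness is tested. This concerns one component of a secondary endpoint. It does not affect the primary pain comparison, and the detailed analysis plan is the natural place to settle it.

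**What to change.** In the detailed analysis plan, for time to adequate anesthesia:

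1. Analyze by randomized arm as a time-to-event endpoint, and define when the clock starts in each arm.
2. Censor topical participants who are not numb at their last negative test or at conversion. Use Kaplan-Meier, or an interval-censored estimator built on the last negative and first positive test times where tests are sparse.
3. Report the proportion numb by the dwell limit and the proportion converted.
4. Compare mean time restricted to the dwell limit in place of the t-test.
5. Exempt this endpoint from the rule that ignores missing data.

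If some participants are converted before the limit, censoring assumes that they would have become numb at the same rate as those still waiting. A sensitivity analysis that carries them as not numb up to the limit covers this.

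The cost is plan wording and a little more analysis. The times of each numbness test and of any conversion must be recorded on the eCRF. If they are not already captured, that is a small addition to data collection.

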### 9.3 Interim Analysis

We will recruit a three member Data Safety and Monitoring Board (DSMB), including a surgeon, an epidemiologist, and a statistician, to review interim analyses for both phases of the study. They will meet before the study begins and then for each of the two interim analyses described below. Meetings will be by teleconference or in-person, as agreed to by the group. Other meetings could be scheduled at the discretion of the DSMB should a problem arise at any point during the conduct of the study. The DSMB will follow guidelines and procedures proposed as part of the DAMOCLES Charter (DAMOCLES Study Group 2005).

This study will include one interim analysis for each phase.

- For Phase I, the interim analysis will be conducted after 40 men have been circumcised using the no-flip technique and had their Shang Rings removed at the 7 day follow-up visit. At the time of the interim analyses, safety, study quality, and possibly some acceptability data will be provided to the DSMB.

The following stopping guidelines are proposed for the DSMB regarding adverse events in the first phase of the study:

1. At the time of the interim analysis, the DSMB may recommend stopping the study or temporarily halting recruitment if there are notably higher rates of severe adverse events than have been seen in previous Shang Ring studies conducted in Africa that will serve as historical control Shang Ring cases (the DSMB will decide the level of significance they will use). In this case, the DSMB may direct that the second phase of the study be conducted using the standard Shang Ring technique.
2. In the event that the interim analysis shows notably fewer moderate and severe adverse events among no-flip Shang Ring cases compared to the standard Shang

Ring technique, the study should continue in order to gather additional data on the no-flip Shang Ring clinical profile, such as time to healing and potential rare adverse events.

- For Phase II, the interim analysis will be conducted after 40 men have been circumcised in each age group in the topical arm (10-15 and over 15 year olds). At the time of the interim analyses, data on reported pain experienced during the circumcision, safety, study quality, and possibly acceptability will be provided to the DSMB by unmasked treatment group. Although this phase is necessarily open-label, the Lead Study Biostatistician will remain blinded to treatment group until the final analyses have been verified. An independent biostatistician, not otherwise involved with Phase II of the study, will prepare the unmasked tables for the DSMB.

The following stopping guidelines are proposed for the DSMB regarding reported pain experienced during the procedure and adverse events in the second phase of the study:

1. At the time of the interim analysis, the DSMB may recommend stopping the study or temporarily halting recruitment if there are notably more severe adverse events among cases using topical anesthesia compared to those using injectable anesthesia (the DSMB will decide the level of significance they will use).
2. In the event that the interim analysis shows notably fewer moderate and severe adverse events among topical anesthesia cases compared to participants receiving standard injectable anesthesia, the study should continue in order to gather additional data on outcomes following use of topical anesthesia with the Shang Ring, such as time to healing and potential rare adverse events.

If the study is stopped temporarily or permanently for any reason, follow-up of participants already enrolled will continue for all the planned follow-up visits; longer if necessary to document complete healing. Enrolled participants will receive continued clinical care as necessary.

It should be noted that if there appears to be an unexpectedly high number of serious adverse events in either phase of the study, any one of the study IRBs may temporarily or permanently halt the study at any time. In addition to IRB oversight, the study clinicians, site PIs and the PEC will review all SAE's as well as severe, related adverse events and closely track other AEs throughout the study.

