## 3.0 ENDPOINTS

### 3.1 Phase I

#### 3.1.1 Primary Endpoints

- We will address the primary objective by evaluating the rate of moderate and severe adverse eventsi (AEs) following Shang Ring MC using the no-flip technique based on clinical exam findings. Other safety endpoints will include documentation of time to complete clinical wound healing,ii device-related malfunctions and occurrences of device displacement.

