## 9.0 STATISTICAL CONSIDERATIONS

### 9.1 Study Size Justification

By recruiting 230 participants into Phase I of the study we expect to have complete follow-up data on at least 200. This sample size number is in line with the recommendations from the World Health Organization for clinical evaluation of MC devices, which is based on an ability to rule out an AE rate of about 5% with a new use of a device that has already been shown to be safe in a larger group of men in RCTs and demonstration studies. (WHO 2012)

In Phase II, by recruiting 345 participants, we expect to have complete follow-up data on at least 300. For comparing postoperative pain scores, we will randomize 345 males in 2:1 ratio to topical vs. injectable anesthesia for circumcision. This sample would provide 100% power to detect a mean difference of 1 on the 0 to 10 pain scale using a 2-sided test at the 0.05 significance level. This calculation assumes a standard deviation of 1.8, which is based on prior data. For other binary endpoints, this sample size will provide at least 80% power to detect absolute differences in proportions between groups of at least 20% separately within each site using two-sided tests at the 0.05 significance level. We will not make any adjustments for multiple comparisons between randomized groups.

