### 9.2 Analysis Plan Summary

A detailed analysis plan that covers both the final analysis and the planned interim analyses will be developed and reviewed and approved internally prior to initiation of the analysis. The following is a summary of the planned analyses for the two phases. Any deviations to be made from this summary plan will be documented in the detailed analysis plan.

In Phase I, the frequency and percentage of men with procedure-related AEs will be tabulated by severity, both overall and by site. Listings of AEs will include information on duration, outcome, severity, and relation to study procedures. Listings of any serious adverse events will also be provided. Shang Ring circumcision and removal procedure data (e.g. time of circumcision and removal, problems encountered, ring sizes used) will be descriptively summarized. Data on operative and post-operative pain, time to return to normal activity, participants' opinions of the Shang Ring procedure and participants' satisfaction with the post-circumcision cosmetic results will be descriptively summarized. Time to complete wound healing will be evaluated using a Kaplan–Meier estimator.

As Phase II is a randomized study of acceptability and safety, primary analyses will be conducted using an as-treated approach (i.e., depending on anesthesia method actually received). However, any deviations between the as-treated approach and a strict intention-to-treat approach will be presented to allow for the assessment of potential biases. Some secondary analyses on safety endpoints may be repeated using an intention-to-treat approach, as relevant.

VAS pain scores will be compared between randomization groups to estimate the efficacy of anesthetic technique at the time of surgery. The frequency and percentage of men with AEs will be tabulated by randomization group, relation to study procedures, and by severity, both pooled across sites and separately within each site. The analysis of AEs will include information on duration, outcome, and relation to study procedures. Stratification by severity will also be considered.

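### The Phase I primary endpoint is moderate plus severe adverse events, but the harm guideline names severe events only, and the summary analysis gives no confidence limit to set against the 5% used for sizing and no age split.

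*Combined protocol and SAP*

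**What the plan says.** Section 3.1.1 meets the Phase I primary objective by "evaluating the rate of moderate and severe adverse events" after no-flip circumcision.

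Section 9.3 has one Phase I look: "the interim analysis will be conducted after 40 men have been circumcised using the no-flip technique and had their Shang Rings removed" at the day 7 visit. Guideline 1 allows the DSMB to recommend stopping or pausing "if there are notably higher rates of severe adverse events than have been seen in previous Shang Ring studies conducted in Africa", at a significance level that it chooses. It continues: "In this case, the DSMB may direct that the second phase of the study be conducted using the standard Shang Ring technique". Guideline 2 says that the study should go on if "the interim analysis shows notably fewer moderate and severe adverse events among no-flip Shang Ring cases".

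Section 9.1 expects at least 200 completers from 230 enrolled. It ties this size to WHO recommendations, "which is based on an ability to rule out an AE rate of about 5% with a new use of a device" already shown to be safe. It gives no severity grade, confidence level or sidedness.

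For the analysis, section 9.2 says that "the frequency and percentage of men with procedure-related AEs will be tabulated by severity, both overall and by site". The only confidence intervals it mentions are for differences between groups, in the paragraph on anesthetic technique. Section 9.2 calls itself a summary of a detailed plan still to be written.

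Section 4.0 recruits equally at ages 10-15 and over 15 because outcomes might differ. Section 1.2 and footnote iv of section 8.2 say that Phase II will use the standard technique if no-flip is not found safe and acceptable, or proves inappropriate.

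**The concern.** Within one section, good news is judged on the primary endpoint and bad news on a narrower one. The grade left out is the one where events have occurred. Table 2 in section 12.3.1 lists 20 moderate and 0 serious events in 1,983 adult placements, and the no-flip pilot in Kenyan boys had 4 moderate and 0 severe in 80. The likeliest kind of excess would therefore not meet guideline 1 as written.

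The final analysis has a matching gap. A percentage below 5% is not the same as having ruled 5% out, and the sizing argument in section 9.1 is about ruling it out. The age strata set up in section 4.0 do not appear in the Phase I safety tables of section 9.2. Phase I informs the technique used for 345 more participants, half of them aged 10-15.

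**Working it through.** **Inputs.** 230 enrolled, 200 completers, 5% to be ruled out (9.1); interim after 40 men (9.3); 20 moderate events in 1,983 placements (Table 2, 12.3.1).

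**The plan's own figures.** Loss is 30/230 = 13.0%, and 200/(1 − 0.13) = 229.9, so 230 reproduces. The 5% can only be checked for consistency. At the historical rate 20/1,983 = 1.0%, about 200 × 0.01 = 2 affected men are expected. The exact upper limit for 2/200 is 3.11% (one-sided 95%) or 3.57% (two-sided 95%). The size is adequate for that scenario.

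**Exact upper limits, n = 200.** With x affected men, the Clopper-Pearson limit is U = the (1 − a) quantile of Beta(x + 1, 200 − x), with a = 0.05 one-sided and a = 0.025 two-sided.

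| x | Percentage | One-sided 95% | Two-sided 95% |
|---|---|---|---|
| 3 | 1.5% | 3.83% | 4.32% |
| 4 | 2.0% | 4.52% | 5.04% |
| 5 | 2.5% | 5.18% | 5.74% |
| 6 | 3.0% | 5.83% | 6.42% |
| 7 | 3.5% | 6.47% | 7.08% |
| 8 | 4.0% | 7.10% | 7.73% |
| 9 | 4.5% | 7.72% | 8.37% |

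So 5% is excluded by at most 4 affected men one-sided, or at most 3 two-sided. From 5 to 9 the percentage is below 5% but neither limit is.

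**How often that happens.** P(5 ≤ X ≤ 9) = F(9) − F(4), with X binomial on 200:

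| True rate | F(9) | F(4) | Difference |
|---|---|---|---|
| 1% | 1.000 | 0.948 | 5% |
| 2% | 0.993 | 0.629 | 36% |
| 3% | 0.919 | 0.281 | 64% |
| 4% | 0.719 | 0.095 | 62% |

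**By age group.** With 100 completers per group, one affected participant already gives an upper limit of 4.66% one-sided or 5.45% two-sided. Age-group intervals can describe but not confirm.

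**The interim guideline.** Suppose 4 of 40 men have a moderate event and none a severe one. That is 10% against 1.0% historically (one-sided Fisher exact p = 0.001 against 20/1,983), yet guideline 1 is not met.

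**What widening guideline 1 would do.** P(2 or more of 40) = 1 − (1 − p)^40 − 40p(1 − p)^39, which is 6% at p = 1%, 34% at 3% and 60% at 5%.

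**The case against.** The strongest objection is that guideline 1 does not alone decide the Phase II technique. Section 1.2 and footnote iv commit the study to the standard technique if no-flip is not found safe or appropriate, with no limit by severity and no tie to the 40-man look. The DSMB receives safety data generally, sets its own significance level, can call extra meetings and is consulted if the phases overlap. The study clinicians, site PIs and PEC track other adverse events throughout. This stands. A reader might infer that an excess of moderate events could not move Phase II off no-flip; the documents do not support that. What remains is that those routes state no criterion.

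Second, naming only severe events for stopping may be deliberate. Phase II guideline 1 has the same form, and halting only for severe harm is defensible. Many historical moderate events were manageable: 8 of the 20 were pain during placement, and the pilot's three wound disruptions healed conservatively. This also stands, and it is why the guideline should stay permissive.

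Third, section 9.2 is only a summary, and anyone can compute an overall interval from a reported count. So one cannot infer that no interval will ever be produced, or that readers could not derive one. But nothing supplied commits the detailed plan to an interval, and tables by site would not give the counts by age.

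Finally, it is tempting to say that 4 events also fail to exclude 5%. That depends on a two-sided limit of 5.04%; one-sided, 4 events do exclude it.

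**Conclusion.** The concern holds as a gap between the primary endpoint, one guideline and the summary analysis. Guideline 1 omits the moderate events that make up most of the expected primary-endpoint events, and section 9.2 neither tests the benchmark in section 9.1 nor uses the age strata. The ambiguous zone is 5 to 9 affected men in 200. It is unlikely at the historical adult rate but more likely than not at a true rate of 3% or 4%.

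This rests on three assumptions. The 5% is read as moderate plus severe, which section 9.1 does not state. There are 200 completers. Table 2 has a serious row but no severe row, so its zero stands in for severe events; it also covers adults only. The pilot's 4/80 (5.0%) is a weak guide to this trial's boys, since only 30 of the 80 were aged 10 to 17.

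A reader might infer that Phase I is too small. The figures do not show that: at a true 1%, the chance of at most 4 affected men, which excludes 5% one-sided, is 95%. Confidence is medium, and the change is worth making because it is specific and cheap.

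**What to change.** 1. In section 9.2, report the Phase I rate of participants with a moderate or severe adverse event with an exact 95% confidence interval, overall and by age group. State whether the limit is one- or two-sided, and read the overall upper limit against the 5% in section 9.1. Label the age-group intervals descriptive. Use the result, as far as data have accrued, for the decision on no-flip in section 1.2 and footnote iv.
2. In section 9.3, extend Phase I guideline 1 to moderate and severe adverse events, and keep it permissive.

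The cost is one interval with an age split and a change of a few words; no participants are added. The downside is that guideline 1 will come up for discussion more often, as the interim probabilities above show, and its historical benchmark comes from adults on the standard technique. The DSMB should weigh that when it sets its criterion, for which the pre-study meeting is a natural occasion ("They will meet before the study begins and then for each of the two interim analyses described below"). A further scheduled DSMB review before Phase II is optional, given its existing power to meet and its consultation role if the phases overlap.
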